**Physical Activity**					
*LAPAQ*	x	x	x	x	x
*Activity Monitor*	x	x	x	x	x
*Activity Diary*	x	x	x	x	x

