**Determinants**					
*Blood pressure*	x		x		x
*Height*	x		x		x
*Body weight*	x		x		x
*Education*	x				
*Employment*	x				
*Alcohol use*	x		x		x
*Smoking*	x		x		x
*Lifetime physical activity*	x				
*Attitude, SS & SE***	x				

** Including tests for spatial working memory*[49], *intra- and extra-dimensional shift performance*[50,51], *paired associate learning performance*[50], *phonemic and semantic word fluency*[52], *and complex figure drawing*[53]

** Only patients in the ParkFit Program

Secondary measures include: (a) physical fitness, measured with the six minute walk test (6MWT)[37]; (b) quality of life, measured with the PDQ-39[38]; and (c) level of physical activity in time and kilocalories per week, measured with the same tri-axial accelerometer that is used as feedback-tool in the ParkFit Program[28]. The level of physical activity is additionally measured with a physical activity diary.

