#### Sample size calculation

Based on the following power considerations, we aimed to include a total of 700 patients. In a small observational study on physical activity in PD, patients scored 45% less on the LAPAQ compared to controls (unpublished data). The coefficient of variation was 110%. Based on a difference of 15% (with coefficient of variation of 110%) between both treatment arms, the study will have at least 80% power (when the correlation between baseline and follow-up measurements is at least 0.50 and when the correlation between the various follow-up measurements is at most 0.85). This is also the power when the correlations are at least 0.60 and at most 0.95, respectively. The power is based on two-sided 95% confidence intervals. We assumed that patients would take part in exercise groups with on average eight participants and that the corresponding ICC would be 0.1. Based on a previous trial of physical therapy for PD involving the national ParkinsonNet networks[21], we expect a drop-out rate of 10%.

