#### Statistical analyses

All participants who really started with their program, will be included in the primary analysis. The results after 6, 12, 18 and 24 months will be evaluated using a linear mixed model with random nested factors 'patient' and 'exercise group'. Fixed factors will be treatment arm, LAPAQ score at baseline, month, month*treatment (interaction), and the factors region, H&Y stage, age, gender and bone density assessment. In an additional analysis, the influence of H&Y stage, age, gender and level of previous sports activities on the success of the treatment will be evaluated by including the interaction terms between treatment and each of these variables in the model. Multiple imputation analyses will be used to evaluate the impact of missing values on the outcome. Throughout, 95% confidence intervals will be calculated.

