## Results

### Inclusion procedure

Selection of patients ran from September 2008 to January 2010. A total number of 4479 patients received a screening questionnaire; 587 (13.1%) did not respond, 439 (9.8%) were excluded because there was doubt about the diagnosis (Figure 2). After invitation for participation, 1766 patients were excluded based on our exclusion criteria, and 1101 eligible patients were excluded because they were not willing to participate. Finally, 586 patients signed informed consent. The number of enrolled patients is less than the power calculation required. However, the power remains over 80% because only 60% of patients participates in exercise groups with an average group size of only three, whereas our power calculation assumed that all patients would participate in exercise in groups of eight patients.

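### The primary model uses baseline LAPAQ as its only activity covariate; adding the baseline monitor and diary could gain some precision, probably modest (minor)

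*Protocol article*

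**What the plan says.** The protocol article states the covariate list of the primary linear mixed model outright (Statistical analyses): "Fixed factors will be treatment arm, LAPAQ score at baseline, month, month*treatment (interaction"), then region, Hoehn and Yahr stage, age, gender and bone density assessment. No other measure of baseline activity is in the list.

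Table 2 marks three physical activity measures at baseline and at every later time point: LAPAQ, the activity monitor and the "Activity Diary". The Secondary endpoints section makes the monitor a secondary measure, reported in both time and kilocalories, and adds: "The level of physical activity is additionally measured with a physical activity diary". The Intervention section places randomization after the baseline assessment.

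The Sample size calculation makes power conditional on how well baseline predicts follow-up. It claims that "the study will have at least 80% power" "when the correlation between baseline and follow-up measurements is at least 0.50" and the correlation among follow-ups is at most 0.85; 0.60 and 0.95 are given as an alternative pair. The primary endpoint is the average of the four follow-up assessments (Primary endpoint section).

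**The concern.** The plan's precision depends on a single self-reported week at baseline, for a variable with a stated coefficient of variation of 110%. Under the protocol's own planning correlations, nearly all the variance that remains after adjusting for that week is stable variation between patients. Averaging four follow-ups cannot remove it, but better baseline prediction can. Two further baseline activity measures are scheduled and unused in the primary model. If either predicts follow-up LAPAQ beyond what baseline LAPAQ already predicts, the confidence interval for the primary effect will be wider than it needs to be. Nothing else is at stake: the treatment estimate is not biased by the omission.

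**Working it through.** **The plan's own figure.** The article gives no figure for the gain from extra covariates. Its nearest figure is the 80% power at 700 patients ("Based on a difference of 15% (with coefficient of variation of 110%) between both treatment arms"), with groups of eight, ICC 0.1 and 10% drop-out. Under 1:1 allocation, analysis of covariance on the four-visit mean and a design effect of 1 + 7 × 0.1 = 1.7, that figure did not reproduce. Power was 38–39% on the raw scale, 47–50% on the log scale with a ratio of 1.15, and 60–62% with a ratio of 0.85. That is a separate matter. The gain below is a ratio of variances and does not depend on it.

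**Inputs from the documents.** Correlation of baseline with each follow-up r0 and among follow-ups r: 0.50/0.85 or 0.60/0.95 (Sample size calculation). Four follow-ups (Primary endpoint). 586 enrolled (Inclusion procedure).

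**Inputs assumed.** For one added baseline measure: r2, its correlation with the follow-up mean, 0.3 to 0.5; r12, its correlation with baseline LAPAQ, 0.3 to 0.7. Neither is in the documents.

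**Step 1: what baseline LAPAQ explains.** The variance of the follow-up mean, in units of a single visit, is (1 + 3r)/4.
- 0.50/0.85: (1 + 2.55)/4 = 0.8875. The correlation of baseline with the mean is r1 = 0.50/√0.8875 = 0.531, so R² = 0.282.
- 0.60/0.95: (1 + 2.85)/4 = 0.9625; r1 = 0.60/√0.9625 = 0.612, so R² = 0.374.

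**Step 2: what is left.** At 0.50/0.85 the residual variance is 0.8875 − 0.25 = 0.6375. Of this, 0.85 − 0.25 = 0.60 (94%) is stable between-patient variance. At 0.60/0.95 it is 0.59 of 0.6025 (98%).

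**Step 3: one added measure.** R² = (r1² + r2² − 2·r1·r2·r12)/(1 − r12²), and gain in effective sample size = (1 − r1²)/(1 − R²) − 1. At the midpoint (r2 = 0.4, r12 = 0.5) under 0.50/0.85: R² = (0.2817 + 0.16 − 0.2123)/0.75 = 0.306; gain = 0.7183/0.6941 − 1 = 3.5%.

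| r2 | r12 | Gain, 0.50/0.85 | Gain, 0.60/0.95 |
|---|---|---|---|
| 0.3 | 0.3 | 3.1% | 2.4% |
| 0.4 | 0.3 | 9.7% | 9.0% |
| 0.5 | 0.3 | 21.6% | 21.3% |
| 0.3 | 0.5 | 0.2% | 0.0% |
| 0.4 | 0.5 | 3.5% | 1.9% |
| 0.5 | 0.5 | 11.4% | 8.7% |
| 0.3 | 0.7 | 1.4% | 5.4% |
| 0.4 | 0.7 | 0.2% | 0.3% |
| 0.5 | 0.7 | 4.7% | 1.7% |

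The gain vanishes where r2 = r1 × r12, because the added measure then carries nothing beyond baseline LAPAQ. Of 586 patients, the midpoint gains are worth 586 × 0.0348 ≈ 20 and 586 × 0.0193 ≈ 11. The interval narrows by 1 − 1/√1.0348 = 1.7% and 1 − 1/√1.0193 = 1.0%.

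**Step 4: both measures.** Assume that each correlates 0.4 with every follow-up, 0.5 with baseline LAPAQ and 0.5 with the other. The residual variance falls from 0.6375 to 0.5925 (7.1%; 586 × 0.6375/0.5925 ≈ 631 patients) or from 0.6025 to 0.5825 (3.3%; about 606).

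**Step 5: the enrolment shortfall in context.** The plan says "we aimed to include a total of 700 patients" and later "Finally, 586 patients signed informed consent", so 114 fewer. The Inclusion procedure section offsets this: only 60% of patients train in groups, of three on average. With clustering in both arms, the planned effective size is 700 × 0.9/1.7 = 371. The achieved design effect is 1 + 0.6 × 2 × 0.1 = 1.12, giving 586 × 0.9/1.12 = 471. With clustering in one arm only, the figures are 630/1.35 = 467 and 527.4/1.06 = 498. In relative terms the offset works.

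**The case against.** The strongest answer is that this is a preference. The model already adjusts for the baseline value of the outcome and for region, stage, age and gender, and declining two further covariates is neither wrong nor contradictory. That stands, and it is why the point is minor.

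Four stronger readings are tempting, and the documents do not support them.

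- *That the trial needs this to make up for 114 missing patients.* The article answers the shortfall with smaller exercise groups, and that argument holds in relative terms. Whether the absolute 80% is right is a different question.
- *That all three instruments measure the same activity.* The Discussion says the questionnaire was preferred because it captures more kinds of activity than the monitor. The difference is partly one of construct, so a strong correlation cannot be taken for granted.
- *That both measures exist for every patient.* A mark in Table 2 does not prove this: DXA carries the same baseline mark, yet Additional measures limits it to a subgroup of 300.
- *That a gain near 20% is likely.* It needs a measure that predicts follow-up LAPAQ almost as well as baseline LAPAQ does (0.50 against 0.531) while correlating only 0.3 with it. At r12 = 0.7, plausible for a diary and a recall, the gain under 0.50/0.85 is 0.2% to 4.7%.

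The covariates already in the model may also absorb part of any gain; the calculation ignores them. On the other side, because the article names its covariates, this is not a detail left to an analysis plan that is not shown. Because baseline precedes allocation, the monitor's later use as a feedback tool in one arm does not compromise its baseline value.

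**Conclusion.** A minor precision point. The primary model leaves unused two scheduled baseline measures of related activity. The possible gain in effective sample size from one of them is about 0% to 22% under 0.50/0.85, and 0% to 21% under 0.60/0.95. The midpoints are about 3.5% (about 20 patients) and about 2% (about 11 patients). Adding both may do somewhat better: 7.1% or 3.3% less residual variance in the middle case.

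Every one of these figures rests on assumed correlations of the added measures, on the protocol's limiting planning correlations rather than observed data, and on baseline values being available for most patients. The gain may be close to zero. A reader might infer that the primary analysis is biased or in error; it is neither.

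**What to change.** Before outcome data are seen, add two fixed covariates to the primary model next to baseline LAPAQ:

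- one baseline activity monitor summary, in time and not kilocalories, so that it matches the primary endpoint;
- baseline diary time.

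State the scale of each. Fill missing baseline values with the overall mean across both arms, so that no patient leaves the analysis; missingness before allocation cannot depend on arm.

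The cost is a short addition to the analysis plan and two degrees of freedom, with no new data collection. In a trial of 586 patients an uninformative covariate costs almost nothing. If the shortfall of 114 is cited in support, cite the article's offset from smaller exercise groups with it.

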## Results

### Inclusion procedure

Selection of patients ran from September 2008 to January 2010. A total number of 4479 patients received a screening questionnaire; 587 (13.1%) did not respond, 439 (9.8%) were excluded because there was doubt about the diagnosis (Figure 2). After invitation for participation, 1766 patients were excluded based on our exclusion criteria, and 1101 eligible patients were excluded because they were not willing to participate. Finally, 586 patients signed informed consent. The number of enrolled patients is less than the power calculation required. However, the power remains over 80% because only 60% of patients participates in exercise groups with an average group size of only three, whereas our power calculation assumed that all patients would participate in exercise in groups of eight patients.

**Figure 2 F2:**
[figure not shown]
**Flow chart of the inclusion procedure**. ** No Parkinson's disease = patient is diagnosed with parkinsonism or patient declared to have no gratifying and sustained response to dopaminergic therapy; ** No sedentary lifestyle = > 3 times a week vigorous-intensity physical activity > 60 minutes; or > 3 times a week moderate-intensity physical activity > 150 minutes; *** Severe disease = H&Y > III; MMSE < 24; severe co-morbidity interfering with daily functioning; use of daily care in an institution; or deep brain stimulation*.

### Baseline characteristics

The most relevant baseline characteristics of included patients are presented in Table 3 and compared with the characteristics of the complete cohort of PD patients and the cohort of patients who were eligible but not willing to participate. Study participants were younger, had a shorter disease duration and were less sedentary compared with eligible patients not willing to participate.

**Table 3 T3:** Characteristics of the invited and included patients

	Complete cohort of PD patients	Eligible patients	
		*Not willing to participate*	*Willing to participate*
**N**	3453	1101	586
**Gender **(% male)	59.0	53.4	65.4
**Age **(years)	66.1 (7.2)	67.2 (7.1)	64.1 (7.6)
**Disease duration **(years)	6.2 (5.7)	6.0 (5.6)	5.3 (4.6)
**Ability to walk **(%)			
*Normal*	814 (23.7)	232 (21.3)	157 (26.8)
*Slow but independently*	1747 (50.8)	556 (51.0)	348 (59.4)
*Independently with walking aid*	605 (17.6)	302 (27.7)	81 (13.8)
*With help of someone*	112 (3.3)		
*Wheelchair bounded*	158 (4.6)		
**Level of physical activity **(min/week)	144.8 (196.7)	40.1 (61.1)	59.2 (71.9)

## Discussion

Several lines of evidence suggest that regular participation in physical activity could be important for patients with PD[47]. The ParkFit trial was designed to evaluate a multifaceted program to achieve an enduring increase in physical activity in PD patients. The intervention is based on accepted motivational and behavioral change models[14,16,17], which will now be employed for the first time in PD.

We carefully monitored the characteristics of all invited patients as well as eligible patients who were not willing to participate. The results demonstrate that among all PD patients who were invited, 64% indeed had a sedentary lifestyle. The results further demonstrate that eligible PD patients not willing to participate were on average somewhat more sedentary in comparison with the participants of the study. Should our study shows a beneficial effect of the ParkFit behavioral change program, efforts must be made to also reach out to this subgroup of sedentary patients.

A critical issue in rehabilitation studies is the choice for an appropriate control condition, and we have selected a program that emphasized safety of movement (according to evidence-based guidelines[32]), rather than the quantity of movements. Both intervention programs are matched for intensity, and are delivered by the same therapists. We have taken several measures to avoid bias between both treatment arms, rendering both groups comparable except for the focus on physical activities. Because the same therapists participate in both programs, differences in their personalities should not differ between the two treatment arms. A possible drawback is contamination. Furthermore, personal preference for a specific program can possibly introduce variation between therapists. We strive to avoid this by: (1) specific training, informing all therapists about the aim of the study and the do's and don'ts in both treatment arms. They have signed a contract and agreed to keep both programs separate. (2) The tools used in ParkFit are not freely available. Since all patients receive their own Activity Monitor and brochure, therapists cannot give these tools to patients allocated to ParkSafe. (3) During the trial, therapists are being visited and observed during one or more sessions. A standardized checklist of prescribed interventions will be completed to investigate if contamination is at play. (4) Each therapist will be interviewed, between 3 to 6 months after start of the program. The aim is to investigate how therapists put the program into practice, and to re-emphasize the do's and don'ts of both programs. (5) About every two months, the research team contacts each therapist to ask them about their individual aims in both treatment arms. Again, it is emphasized that coaching towards a more physically active lifestyle is not allowed in ParkSafe. (6) Yearly, a 'booster' session is planned for therapists to discuss possible problems and to re-emphasize the do's and don'ts.

A strong element of the ParkFit trial is the availability of our national ParkinsonNet networks[21], which allows us to administer the interventions in both treatment arms by therapists with documented experience in treating PD patients. The ParkFit trial is one of the largest and longest lifestyle intervention trials in PD, and is the first one to focus on behavioral change as an intermediate to achieve a sustained increase in physical activity levels.

The endpoints of this trial cover several complementary domains. A prerequisite is that patients will actually increase their physical activity levels. To document this, we have selected the time spent on physical activities per week as primary endpoint. We choose the LAPAQ as primary outcome measure instead of the Activity Monitor because a questionnaire covers a wider range of activities[48].

We also want to see whether physical activity affords any symptomatic relief of PD. To this end we have included a battery of additional endpoints (including quality of life) that measure possible health benefits for patients. Safety is also an issue, because physical activity may theoretically predispose patients to falls. Therefore, this will also be documented in this study. Furthermore, costs will be recorded, although we have no specific a priori reason to expect drastic increases or reductions in costs associated with the interventions of this trial.

In conclusion, the ParkFit trial is expected to yield important new knowledge about behavioral interventions for patients with PD to change their sedentary lifestyle. If the ParkFit Program shows good treatment compliance and beneficial symptomatic effects, future trials could identify which components of our multifaceted approach are most effective. In addition, positive results may have implications for different neurological disorders where beneficial effects of physical activity may be expected. The results of the ParkFit trial are scheduled for 2012.
